## Discussion

Anastomotic leakage is the predominant surgical complication after esophagectomy [1]. The cause of an anastomotic leakage is multifactorial [7, 8]. One of these factors includes hypovascularization of the gastric conduit which opposes healing of the anastomosis and consequently contributes to leakages. In retrospective analyses of both participating centres of the current study, major calcifications of the aorta and celiac axis have been shown to be an independent risk factor for anastomotic leakage [20, 21]. The preoperative identification of patients at risk for anastomotic leakage allows for personalized treatment programs. The ISCON trial is a safety and feasibility study aiming to stimulate the vascularisation of the gastric conduit prior to the esophagectomy in selected patients. Patients at high risk for anastomotic leakage are selected via calcification scores on preoperative CT-scans.

### Efficacy ISCON

Several studies have investigated the efficacy of ISCON. A recent meta-analyses published in 2020 showed that ISCON seems to reduce the incidence and severity of anastomotic leakage [22]. Yet ISCON failed to demonstrate a significant reduction of leakage precentages in other meta-analyses and systematic reviews of clinical studies [16, 23, 24]. One explanation for this controversy could be the fact that multiple factors contribute to the development of anastomotic leakage ensuing that ISCON alone might not have enough impact to significantly decrease anastomotic leakage numbers. However, this discrepancy could also be explained by the heterogeneity and retrospective nature of the studies. The heterogeneity is caused by several factors including the selection of patients, the time interval between ISCON and esophagectomy, which arteries are occluded and the technique that is used for ISCON (radiological versus laparoscopic). These factors could have influenced the efficacy and are discussed separately in the consecutive paragraphs.

### Selection of patients

The majority of the studies reporting on ISCON did not select patients [24]. In the current study, the UCS for major calcifications of the thoracic aorta was used as an indicator of poor generalized cardia vascular status. The location of thoracic aorta was internally and externally validated as a predictor for anastomotic leakage after esophagectomy in 3 studies [13, 20, 25].

### Interval

Another discussion point is the interval between ISCON and esophagectomy which has been widely discussed in the literature [24]. On the one hand, the interval should be long enough to redistribute the blood flow of the stomach. On the other hand, the interval should be short enough to avoid hindering the esophagectomy due to potential adhesions or causing a delay in the treatment. In the literature, intervals range between 4 and over a 100 days. Increasing evidence is available arguing for an interval of 2 weeks. Animal studies have demonstrated that immediately after ISCON, the gastric perfusion drops to 20–30%. After 1 week, the gastric perfusion around 60% and 2 weeks after ISCON, the gastric perfusion is over 90% [26, 27]. In addition, a recent meta-analysis compared the studies with an interval of > 2 weeks versus < 2 weeks and showed a trend towards lower leakage percentages for > 2 weeks, whereas no reduction in leakages was seen for < 2 weeks [22]. In addition, an interval of 2 weeks is likely to be short enough to prevent the development of adhesions. In order to minimalize adhesions, ISCON procedure is kept as lean as possible and no further preparations for the esophagectomy will be performed during the first operation. The presence of adhesions during esophagectomy will be scored accordingly to the Peritoneal adhesion index [28].To take into account for logistics, as scheduling surgeries and weekends, an interval of 12 till 18 days between ISCON and esophagectomy is used in the current trial.

### Radiological versus surgical ISCON

In the current study, ISCON is performed by occluding the left gastric, left gastroepiploic and short gastric arteries in an attempt to achieve a maximum ischemic effect. In contrast, some of the retrospective studies occluded only the left gastric artery [24]. Furthermore, ISCON could be performed radiologically as well as surgically. Superiority of one technique over the other has not yet be demonstrated. In the current study, ISCON will be performed laparoscopically since our study team already has experience with this procedure. In addition, a potential benefit of surgical ISCON is the precise and certain occlusion of the target arteries. Radiologically, it could be more difficult to selectively occlude the short gastric arteries. Instead of the short gastrics, the splenic artery could be partly embolized with a risk of splenic ischemia [29]. Furthermore, surgical ISCON allows for a translational arm with ICG measurements. Advantages of radiological ISCON are that it can be performed under local anesthesia and it does not cause adhesions.

### Safety ISCON

A meta-analysis on ISCON was published in 2017 including 11 retrospective studies and a combined total of 1152 patients. None of the included studies reported any major complications associated with the ISCON procedure itself [16]. This indicates that this procedure can be safely performed in unselected patients. Furthermore, since major calcifications of the thoracic aorta according to the UCS score have a relatively high prevalence (30%), we postulated that this meta-analysis likely also include a proportion of patients with major aortic calcification, and that ISCON could thus also be safe in these selected patients [13]. None of the retrospective studies reported perforation due to ischemia after ISCON. Hence, we will remain vigilant for this complication, but deem the chance of it occurring slim. Based upon prior clinical experience in the University Hospital of Cologne, we expect gastroparesis to occur in up to 25% of patients. Since patients with gastroparesis could be at an increased risk of acquiring an aspiration pneumonia, patients’ intake and complaints as nausea and vomiting will be closely monitored and gastroparesis will be treated by emptying the stomach via nasogastric tube placement. None of the retrospective studies report on gastroparesis and nutritional intake after ISCON. This could be explained due to the retrospective data collection. In the current study we use a clear definition of gastroparesis and will prospectively collect nutritional intake data which strengthen the study. Importantly, as mentioned, the meta-analysis included only retrospective studies and had a high degree of heterogeneity with regards to selection of patients, the time interval between ISCON, which arteries are occluded and the technique that is used for ISCON (radiological versus laparoscopic) [22]. The safety and feasibility of ISCON in selected patients have not yet been demonstrated in a prospective trial.

## Conclusion

In summary, the ISCON trial is a single-arm prospective study investigating the safety and feasibility of laparoscopic ISCON 12–18 days prior esophagectomy in a highly selected group of patients at risk to develop an anastomotic leakage. In addition, a translational program is set up to assess the postulated effect of laparoscopic ISCON. The ISCON trial is unique with respect to its prospective study design and the careful selection of eligible patients by means of atrial calcifications. If the hypothesis is confirmed that ISCON is safe and feasible, a randomized controlled, multicentre trial will be set up to determine whether esophagectomy preceded by ISCON is superior over esophagectomy without ISCON in terms of anastomotic leakage.

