To date, several studies reported ISCON to be safe in esophageal surgery and its possible efficacy in decreasing anastomotic leakage [15, 16]. However, all studies were retrospective and performed in unselected patients. Therefore, the current prospective safety and feasibility trial aims to investigate the feasibility and safety of performing laparoscopic ISCON for esophageal cancer in patients at high-risk for anastomotic leakage, as based upon their vascular status on pre-operative CT scans (defined by the UCS of the thoracic aorta and modified NASCET score of the celiac axis). The hypothesis of this study is that in these selected patients with an increased risk of vascular impairment of the gastric tube, laparoscopic ISCON is feasible and can be safely performed prior to esophagectomy.

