### Primary outcome

Complications are defined according to the Esophageal Complications Consensus Group (ECCG) and graded according to the Clavien Dindo Classification [1, 17]. The primary outcome measure is the percentage of complications grade ≥ 2 occurring during or after ISCON and before esophagectomy.

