### Sample size

This is a prospective single arm safety and feasibility trial, classified as a “stage 2a Development” study according to the IDEAL recommendations for surgical innovation [19]. Based upon these recommendations, a total of 20 subjects will be included and no formal sample size calculations are performed (10 patients per centre).

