### Statistical analyses

Statistical analyses in this study are primarily based on descriptive means. Categorical data will be summarized as frequencies. Normally distributed continuous data will be summarized as means with corresponding standard deviations. Non-normally distributed continuous data will be summarized as medians with corresponding interquartile ranges. Repeated outcomes at various time points (such as translational outcomes and PROMS) will be presented descriptively and tested as paired measurements analysis will be performed with SPSS software (IBM).

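### The next trial depends on safety being confirmed, but no limit on the primary complication rate at 20 patients says what would confirm it

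*Protocol article*

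**What the plan says.** The Background section of the protocol article gives the hypothesis for the selected patients: "laparoscopic ISCON is feasible and can be safely performed prior to esophagectomy". The Conclusion attaches a decision to it: "If the hypothesis is confirmed that ISCON is safe and feasible, a randomized controlled, multicentre trial will be set up".

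The outcome that bears on this is defined under Primary outcome: "The primary outcome measure is the percentage of complications grade ≥ 2 occurring during or after ISCON and before esophagectomy". Under Sample size, "a total of 20 subjects will be included and no formal sample size calculations are performed". The number is taken from the IDEAL stage 2a recommendations and split equally between two centres. Under Statistical analyses: "Statistical analyses in this study are primarily based on descriptive means. Categorical data will be summarized as frequencies". The only testing mentioned there is of paired measurements for repeated outcomes, such as the translational measures and patient-reported outcomes.

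Numeric safety limits appear only under Interim analysis. After the first 10 patients, the rules are met if more than 40% have a gastric perforation that needs re-intervention, more than 40% have aspiration pneumonia that lengthens the stay, or more than 40% cannot have their esophagectomy within 30 days because of ISCON complications. The monitoring section adds ongoing surveillance by an independent Medical Safety Officer, with a review of serious adverse events after the first five esophagectomies.

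**The concern.** To confirm a hypothesis, some possible result must count as failing to confirm it. The article states a safety hypothesis and makes a randomized trial conditional on it. It does not say what final rate of grade 2 or higher complications would be too high. The interim rules do not supply this, because they address three other events at half the sample.

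Two things are at stake. The judgement of safety would be made after the data are seen. A low count in 20 patients could also be taken as established safety when it still allows rates that matter. The section Safety ISCON already reasons in this way: it takes the absence of reported major complications in retrospective series as an indication that the procedure is safe.

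**Working it through.** **Inputs from the article.** N = 20, as 10 per centre (Sample size). Primary outcome and its analysis as a frequency (Primary outcome, Statistical analyses). Three interim limits of more than 40% in the first 10 patients (Interim analysis). Expected gastroparesis up to 25% (Safety ISCON). No acceptable rate, error level or power is stated.

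**The plan's own figure.** 2 centres × 10 = 20, which agrees. With no rates or error levels given, nothing further can be reproduced.

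**Assumption on the unit.** The primary outcome is worded as a percentage of complications. The calculation below takes the patient as the unit: x is the number of patients with at least one grade 2 or higher complication, out of n = 20.

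**Precision at n = 20.** The exact Clopper-Pearson 95% limits are

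- lower = 2.5% quantile of Beta(x, n − x + 1), or 0 if x = 0;
- upper = 97.5% quantile of Beta(x + 1, n − x).

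The one-sided 95% upper bound uses the 95% quantile instead. For x = 0 the upper limits reduce to 1 − 0.025^(1/20) = 0.168 and 1 − 0.05^(1/20) = 0.139.

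| Patients with event | Observed | Two-sided 95% interval | One-sided 95% upper bound |
|---|---|---|---|
| 0/20 | 0% | 0 to 16.8% | 13.9% |
| 1/20 | 5% | 0.1 to 24.9% | 21.6% |
| 2/20 | 10% | 1.2 to 31.7% | 28.3% |
| 4/20 | 20% | 5.7 to 43.7% | 40.1% |
| 5/20 | 25% | 8.7 to 49.1% | 45.6% |
| 10/20 | 50% | 27.2 to 72.8% | 69.8% |

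The article's expected gastroparesis rate, 25% of 20, is 5 patients. It does not say whether these would be graded 2 or higher. If they were, the result would be compatible with about 9% to 49%, and the article does not say whether that confirms the hypothesis.

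**What the interim rules exclude.** More than 40% of 10 means at least 5 patients with the same named event. The chance that one rule is met is P(X ≥ 5), with X binomial (10, p):

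| True rate of that event | Chance the rule is met |
|---|---|
| 10% | 0.2% |
| 20% | 3.3% |
| 30% | 15.0% |
| 40% | 36.7% |
| 50% | 62.3% |

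Up to 4 of 10 with a named event passes. Other grade 2 or higher complications count towards no rule unless they push the esophagectomy past 30 days.

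**What a sponsor-chosen ceiling would mean.** The article gives no ceiling, so these are assumed values that show the range, not recommendations. The rule is that the one-sided 95% upper bound must lie below the ceiling.

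| Assumed ceiling | Most patients with an event | Chance of passing if true rate is 10% | Chance of passing if true rate is 25% |
|---|---|---|---|
| 20% | 0 | 12.2% | 0.3% |
| 30% | 2 | 67.7% | 9.1% |
| 40% | 3 | 86.7% | 22.5% |
| 50% | 5 | 98.9% | 61.7% |

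Which results count as confirmation depends heavily on a number that the article does not state.

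**The case against.** The strongest reply is that this is openly a descriptive IDEAL stage 2a study. Such a study needs no formal test or power calculation, and the article does not pretend otherwise. The sentence in the Conclusion looks forward and is not a decision rule in the Methods. The abstract's Discussion is softer and says only that the need for a randomized trial depends on the results. An exact interval is a detail commonly left to an analysis plan, which is not shown, and describing the analyses as primarily descriptive does not exclude one. Most of this stands. The absence of an interval is therefore not the defect. What remains is that the article uses the language of confirmation and states no limit on its primary outcome to support it.

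A reader might infer that the plan has no criterion at all, so that any result could be called safe. The documents do not support that. The three interim rules rule out some extreme early results, and the Medical Safety Officer reviews serious adverse events. The rules are lenient, concern other events and do not apply at 20 patients, but they exist.

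A reader might also take 40% as the article's unacceptable rate and derive a limit of 3 patients in 20. That is not supported either. The 40% is an early stopping limit for three specific events at 10 patients, not a bound on all grade 2 or higher complications at 20. If gastroparesis at the expected upper rate of 25% were graded 2 or higher and made up the whole event rate, such a rule would fail with probability 1 − 0.225 = 0.775.

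**Conclusion.** The point holds in a limited form. The article makes a randomized trial conditional on confirmed safety, but sets no end-of-study limit on the grade 2 or higher complication rate, and its only numeric limits concern other events at the interim look. The frequency alone does not show how little 20 patients can exclude: no events still allows a rate up to 16.8%, and five events allow 8.7 to 49.1%.

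These figures assume the patient as the unit, 20 evaluable patients and exact binomial limits. The design and data remain usable. The weakness lies in what may be concluded, so the change should be made but does not put the trial itself in question.

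**What to change.** Define the primary result as the proportion of patients with at least one grade 2 or higher complication between ISCON and esophagectomy, and report it with an exact (Clopper-Pearson) 95% interval. In the Conclusion, replace the language of confirmation with a statement that the trial estimates this rate, and give the precision at n = 20: 0/20, 0 to 16.8%; 2/20, 1.2 to 31.7%; 5/20, 8.7 to 49.1%.

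If the sponsor prefers to keep the language of confirmation, it should state its own maximum acceptable rate before the data are seen, to be compared with the upper confidence bound, together with the chance of passing at plausible true rates. The interim 40% should not be carried over as that rate.

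Either route takes a few sentences and no additional patients. The cost is that the possible safety claim becomes visibly weaker.

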## Data Availability

The dataset of this study will be available from the corresponding author on reasonable request after completion.

## Abbreviations

CT: Computed tomography
DSMB: Data Safety Monitoring Board
EOCG: European Clinical Oncology Group
FDG-PET: [18F] Fluorodeoxyglucose positron emission tomography
GEJ: Gastro-esophageal junction
ICG: Indocyanine green
ISCON: Ischemic conditioning
NASCET: North American Symptomatic Carotid Endarterectomy Trial
METC: Medical research ethics committee (MREC); in Dutch: medisch ethische toetsing commissie (METC)
CDC: Clavien-Dindo Classification of surgical complications
(S)AE: (Serious) Adverse Event
UCS: Uniform calcification score
